### Primary and secondary outcomes

The primary endpoint will be the complete occlusion rate at 6-month follow-up.

Secondary endpoints will include:

1. Immediate technique success rate.

2. Overall morbidity or mortality (assessment time point: 30 days, 90 days and 1 year post-operation).

3. Ischemic stroke or intracranial bleeding (assessment time point: 30 days, 90 days and 1 year post-operation)

4. The rate of intra-stent stenosis (assessment time point: 6 months post-operation)

5. The rate of intra-stent thrombosis (assessment time point: 6 months post-operation)

6. General adverse events (assessment time point: 30 days, 90 days and 1 year post-operation).

### Participants

#### *Inclusion criteria*

Patients eligible for inclusion will meet the following criteria:

1. Age 18 years to 75 years, male or nonpregnant female.

2. Unruptured internal carotid artery or vertebral artery saccular aneurysm (including recanalized aneurysms), confirmed by CTA, MRA, or DSA.

3. Width of aneurysm neck ≥4 mm, and aneurysm size ≥10 mm.

4. Parent vessel with a diameter range of 2.0-6.5 mm.

5. Indications for Enterprise stent-assisted coiling and Tubridge FD implantation with or without coiling.

6. Is willing to return to the investigational site for follow-up according to our protocol.

7. Understands the nature of the procedure and provision of written informed consent.

#### *Exclusion criteria*

Patients will be excluded if they meet any of the following criteria:

1. No appropriate route to access the aneurysm via endovascular approach.

2. A non-treated arteriovenous malformation (AVM) in the territory of the target aneurysm.

3. Ruptured aneurysms.

4. Anatomy not appropriate for endovascular treatment due to severe intracranial vessel tortuosity or stenosis, or intracranial vasospasm not responsive to medical therapy.

5. Major surgery within the previous 30 days or planned within the next 90 days after the enrollment date.

6. Severe neurological deficit that renders the patient incapable of living independently (modified Rankin score ≥4).

7. Co-morbid conditions that may limit survival to less than one year.

8. Enrollment in another trial.

9. Poor compliance (inability to complete the full study).

10. Allergy or contraindication for the use of nickel-titanium alloy.

11. Inability to receive anti-platelet or anticoagulant medication.

12. History of life-threatening allergy to contrast dye.

#### *Withdrawal criteria*

Patients who have been included in this trial and have given written informed consent but are not able to complete the whole study for any reason will be withdrawn, including circumstances as below:

1. The subjects voluntarily quit the trial for various reasons.

2. Occurrence of serious adverse events. The subjects, main researchers, ethics committee, supervisor or CFDA terminate the research based on the consideration of ethics.

3. Early termination of the process based on the investigator’s judgment (to prevent development of severe complications, and so on).

4. Significant deviation in implementation, or the subject failed to comply with the protocol.

5. Lost of follow-up due to changes in working/living places, or fortuitous accident. When these fortuitous accidents occurs, including traffic accident, death,or bone fracture, et al., Close follow-up should be conducted to determine their relationship with the usage of Tubridge FD.

6. flawed or absence of informed consents.

When the subjects are withdrawn, the researcher would try their best to contact the subjects via telephone call, letter, clinic interview, et al., and document the reasons why they are withdrawn in detail; of which, those experienced adverse effects must be recorded in the CRF if the adverse effects were thought related to the devices used in this trial. All raw data of those enrolled and treated subjects must be kept including subjects withdrawn.

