### Planned analyses

Statistical analyses will be conducted based on an intention-to-treat (ITT) population. Participants who are recruited and treated will be considered the full analysis set (FAS), those who complete treatment and the entire follow-up protocol will be considered the per-protocol set (PPS), and those who are treated and have at least one safety evaluation will be considered the safety set (SS). Last observation carried forward (LOCF) method will be implemented to handle the missing data from withdrawn subjects, who would be included in FAS.

Comparisons of demographic information will first be conducted to measure the balance between the two groups. Then evaluation of primary and secondary outcome will conducted as below:

Primary outcomes:

The comparison of the treatment groups with regard to the primary endpoint will be performed with the data of the Full Analysis Set as well as of the Per Protocol Set. In case the two analyses will lead to different conclusions the result of the analysis of the Per Protocol Set is deciding.

Use superiority test for analysis of primary outcome. The formal test problem is as follows:

Test problem for the complete occlusion rate at 6-month follow-up:

Let πT be the rate of complete occlusion rate of treatment group at 6-month follow-up.

Let πc be the rate of complete occlusion rate of control group at 6-month follow-up.

The superiority margin δ is 0.

Test problem:

H0: πT -πc ≥ 0

H1: πT -πc < 0

α = 0.05 (2-sided)

The alternative hypothesis will not be accepted unless the lower limit of the 95% confidence interval of the difference of occlusion rate lies above the superiority margin.

Secondary outcomes:

Immediate occlusion rate will be conducted in FAS group, while other safety evaluation will be be conducted in SS group. For quantitative data, t-test (for equal variances and normal distribution) or Wilcoxon rank sum test could be applied according to the distribution of the data. The categorical variables will be compared between study arms using Chi-square tests or Fisher's exact tests (if Chi-square test is not valid). Besides, for immediate technique success rate, 95% confidence interval of each groups and difference between groups will be estimated.

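### The withdrawal criteria do not separate serious adverse events, early termination and deviations from leaving follow-up, so outcomes of these patients may be lost under an intention-to-treat label

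*Protocol article*

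**What the plan says.** The Withdrawal criteria open with patients who "are not able to complete the whole study for any reason will be withdrawn, including circumstances as below". Three of the six listed circumstances are not a patient's own choice to leave, a loss of contact or a consent defect:

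- Item 2: "Occurrence of serious adverse events. The subjects, main researchers, ethics committee, supervisor or CFDA terminate the research", on ethical grounds.
- Item 3: "Early termination of the process based on the investigator’s judgment", with the explanation "to prevent development of severe complications, and so on".
- Item 4: "Significant deviation in implementation, or the subject failed to comply with the protocol".

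Once a patient is withdrawn, researchers must try to make contact (telephone, letter or clinic interview) and "document the reasons why they are withdrawn in detail". Adverse effects "must be recorded in the CRF if the adverse effects were thought related to the devices used in this trial". Raw data of treated subjects are kept. Close follow-up is asked for after accidental events, a group that includes death, to judge their relation to the Tubridge device. No 6-month DSA and no 1-year evaluation is required after withdrawal.

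Table 1 ticks the withdrawal criteria during the procedure and at 30 days, 90 days, 6 months and 1 year.

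Planned analyses states: "Statistical analyses will be conducted based on an intention-to-treat (ITT) population". It then defines the full analysis set (FAS) as recruited and treated patients, and the per-protocol set (PPS) as those who complete treatment and all follow-up. Missing data of withdrawn subjects in the FAS are filled by last observation carried forward (LOCF). If FAS and PPS disagree on the primary endpoint, the PPS decides. The Sample size section allows for up to 20% withdrawn.

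**The concern.** A complication, a deviation from protocol and an exit from follow-up are three different things, and the list treats them alike. Both treatments are implanted in one procedure, so a patient who has had a serious adverse event or a deviation can in principle still be observed at 6 months and 1 year. If such patients are withdrawn instead, the missing outcomes fall in a group whose results probably differ from the rest, and at different rates by arm if complications or failed deployments differ. The Background itself asks whether ischaemic complications are more frequent with flow diverters.

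Two results are at stake. The first is the 6-month complete occlusion rate, which could be compared in a selected group. The second is the set of 1-year endpoints (morbidity or mortality, ischaemic stroke or intracranial bleeding, general adverse events). These carry no condition on device relation, yet after withdrawal only adverse effects thought device-related must be recorded. An analysis plan cannot recover outcomes that were not collected.

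**Working it through.** **1. The plan's own figures.** Inputs from the Sample size section: 35% v 65%, two-sided α = 0.05, power 0.80, 1:1. The continuity-corrected two-proportion formula gives 49 per arm (98). Allowing for 20% withdrawn, 49 / 0.80 = 61.25, rounded up to 62 per arm (124). Both figures reproduce. The allowance equals 0.20 × 62 = 12.4, about 12 patients per arm, for withdrawals of all kinds.

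**2. What fills the gap for a withdrawn patient.** The schedule has a DSA during the procedure and one at 6 months. For a patient withdrawn before 6 months, LOCF can carry forward only the procedural angiogram. Under Safety and efficacy assessment, that image is graded by flow modification for Tubridge alone and by the Raymond classification when coils are used. In the PPS the patient is absent.

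**3. Bias in a completers-only comparison.** Let p be the true occlusion rate (equal in both arms), s the share withdrawn and q the occlusion rate among the withdrawn.

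Observed rate among completers = (p − s·q) / (1 − s)

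Completers per arm = 62 × (1 − s), rounded. A false superiority claim means that the lower Wald 95% limit of the difference (Tubridge minus control) exceeds 0. Its probability comes from exact enumeration of the two binomials. All values of p, s and q below are assumptions, except that 35% is the protocol's control rate.

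For the first scenario: Tubridge (0.50 − 0.15 × 0.20) / 0.85 = 0.553; control (0.50 − 0.05 × 0.20) / 0.95 = 0.516.

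| p | s, Tubridge v control | q | Completers | Observed rates | False superiority |
|---|---|---|---|---|---|
| 50% | 0 v 0 | – | 62 v 62 | 50.0% v 50.0% | 2.9% |
| 50% | 15% v 5% | 20% | 53 v 59 | 55.3% v 51.6% | 6.5% |
| 50% | 20% v 5% | 0% | 50 v 59 | 62.5% v 52.6% | 18.8% |
| 35% | 20% v 5% | 0% | 50 v 59 | 43.8% v 36.8% | 11.1% |
| 35% | 15% v 5% | 20% | 53 v 59 | 37.6% v 35.8% | 4.4% |
| 50% | 8% v 5% | 20% | 57 v 59 | 52.6% v 51.6% | 3.3% |
| 50% | 10% v 10% | 20% | 56 v 56 | 53.3% v 53.3% | 2.4% |
| 50% | 5% v 15% | 20% | 59 v 53 | 51.6% v 55.3% | 1.0% |

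**4. The same 15% v 5% scenario in the FAS.** If every withdrawn patient is carried forward as non-occluded, the rates are 0.50 − 0.15 × 0.20 = 0.47 and 0.50 − 0.05 × 0.20 = 0.49, with 62 per arm. The chance of a false claim is 1.7%. The inflation therefore belongs to the completers-only set, and it matters because that set decides when the two disagree.

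**The case against.** A reader might infer that every patient with a serious adverse event is removed and that these outcomes are lost by design. The text does not go that far. The opening sentence concerns patients unable to complete the study, and item 2 can be read as applying only when a party ends participation. In item 3, the word process may mean the procedure or study participation. The parties named in item 2 include the subject, the ethics committee and the regulator, so these are not all decisions of unblinded site staff. Table 1 schedules clinical evaluation and the 6-month DSA without exempting patients who have had an event. This objection stands: withdrawal is permitted, not shown to be automatic.

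A reader might also infer that the complication itself disappears from the safety results. It does not. Serious adverse events must be reported within 24 hours, and a treated patient with one safety evaluation stays in the safety set. Only events after withdrawal are at risk.

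A third tempting reading is that the plan is shown to favour Tubridge. The documents give no withdrawal rates by arm. The single-centre study in the Background reports no procedure-related morbidity or mortality. The direction depends on which arm loses more patients, and part of the effect on the primary endpoint comes from the rule that the PPS decides, which is a separate matter.

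Finally, this is a condensed article, and the full protocol may say more about follow-up after withdrawal. That tempers the point but does not remove it, because the list and the duties after withdrawal are stated explicitly. None of them calls for the 6-month DSA or the 1-year evaluation.

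**Conclusion.** The point holds as a defect of wording with consequences for the primary and 1-year outcomes. As written, the criteria allow patients with serious adverse events, early termination or deviations to leave follow-up, and require no later outcome from them. That conflicts with the intention-to-treat statement, and neither LOCF nor the PPS repairs it.

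The size is not established. In the completers-only set, the chance of a false superiority claim is 6.5% or 18.8% under the two unequal-withdrawal scenarios at a true rate of 50%, against 2.9% with no withdrawals. It is 1.0% to 3.3% when rates are near-equal, equal or reversed. All of these rest on assumed withdrawal rates and assumed occlusion among the withdrawn. The change should be made, but the documents do not show that the trial's conclusion would be biased without it.

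**What to change.** Reword the Withdrawal criteria so that:

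- items 2 to 4 are recorded as events or deviations and do not by themselves end follow-up;
- these patients stay in their randomised arm and are invited to the scheduled contacts and the 6-month DSA, unless consent is withdrawn or the DSA is judged clinically unsuitable;
- patients without a DSA are still followed for vital status, stroke and bleeding to 1 year;
- all adverse events are recorded, whatever their judged relation to the device.

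Decisions on stopping treatment, and termination by the ethics committee or the regulator, are left as they are. The cost is a protocol amendment and continued use of planned visits for a few patients. No new procedure is added, and the calculated sample size does not change. The article reports that recruitment is open, so the change can still take effect.

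### Death is filed under loss to follow-up, so a patient who dies before the 6-month angiogram is scored by carry-forward in the FAS and dropped from the deciding PPS

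*Protocol article*

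**What the plan says.** All places are in the protocol article.

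- **Withdrawal criteria, opening sentence:** enrolled patients who "are not able to complete the whole study for any reason will be withdrawn".
- **Withdrawal criteria, item 5:** "Lost of follow-up due to changes in working/living places, or fortuitous accident. When these fortuitous accidents occurs, including traffic accident, death,or bone fracture". The item goes on to ask for close follow-up to establish any relationship with the Tubridge device.
- **Withdrawal criteria, closing paragraph:** adverse effects in withdrawn patients "must be recorded in the CRF if the adverse effects were thought related to the devices used in this trial". Contact attempts are required, and raw data of treated patients are kept.
- **Primary and secondary outcomes:** "The primary endpoint will be the complete occlusion rate at 6-month follow-up". Secondary item 2 is "Overall morbidity or mortality (assessment time point: 30 days, 90 days and 1 year post-operation".
- **Planned analyses, FAS:** "Last observation carried forward (LOCF) method will be implemented to handle the missing data from withdrawn subjects, who would be included in FAS".
- **Planned analyses, PPS:** "those who complete treatment and the entire follow-up protocol will be considered the per-protocol set (PPS"). If the FAS and PPS lead to different conclusions, the PPS result decides.
- **Safety and efficacy assessment:** the immediate result is graded on the Raymond scale when coils are used, and by flow modification when the diverter is used alone. Table 1 schedules DSA only during the procedure and at 6 months.

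**The concern.** A death is an observed outcome. Filing it beside house moves and fractures turns it into missing data, and the analysis section then has a fixed rule for missing data. The 6-month status of a patient who has died is taken from an image made at the end of the procedure, or the patient is left out. In neither set does the death itself determine the score.

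The primary comparison is at stake. Deaths could differ in number between a diverter and stent-assisted coiling, and the protocol's Background raises hemorrhagic and ischemic complications of diverters as open questions. The PPS can then overrule the FAS after the deaths have been removed from it. Replacing LOCF with another imputation method would not cure this: while death counts as a withdrawal, any method would still invent a 6-month occlusion status for a patient who has died.

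**Working it through.** **1. The plan's own figure.** Inputs from Sample size: 35% v 65%, two-sided α = 0.05, power 0.80, 20% withdrawals.

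- Uncorrected: n₀ = [1.96·√(2·0.5·0.5) + 0.8416·√(0.35·0.65 + 0.65·0.35)]² / 0.30² = 42.4, so 43 per arm.
- With continuity correction: (n₀/4)·[1 + √(1 + 4/(0.30·n₀))]² = 48.9, so 49 per arm.
- 49/(1 − 0.20) = 61.25, so 62 per arm and 124 in total.

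The stated 98 and 124 reproduce. The arithmetic is not in question. Deaths fall within the 20% allowance because they are classed as withdrawals.

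**2. Following the rules for a patient who dies.**

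| Time of death | FAS | PPS |
|---|---|---|
| Before 6-month DSA, procedure image complete | Success, carried forward | Dropped |
| Before 6-month DSA, procedure image shows filling | Failure, carried forward | Dropped |
| After observed 6-month DSA, before 1 year | Observed result | Dropped, because follow-up is not complete |

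No angiogram is scheduled between the procedure and 6 months, so the carried-forward value would normally be the procedure image. Taking the Raymond scale to include a complete grade, coiled sacs can carry forward a success. Diverter-alone sacs have only a flow-modification description, so the rule can act differently by arm.

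**3. Size per death.** The documents give no death rate. Assume 1 to 4 re-scored deaths in one arm of 62: 1/62 = 1.6 points, 2/62 = 3.2, 4/62 = 6.5, against a planned difference of 65 − 35 = 30 points.

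**4. Can the conclusion change?** Assumed illustration: 62 per arm, 5 deaths on treatment and 1 on control before 6 months, no other losses. The 95% CI is d ± 1.96·√[p₁(1−p₁)/n₁ + p₂(1−p₂)/n₂].

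Borderline case, survivors near 55% v 35%:

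| Handling of deaths | Counts | Difference | 95% CI | Lower limit above 0? |
|---|---|---|---|---|
| Excluded (as in PPS) | 31/57 v 21/61 | 0.200 | 0.024 to 0.375 | Yes |
| Failures | 31/62 v 21/62 | 0.161 | -0.010 to 0.333 | No |
| LOCF, all successes | 36/62 v 22/62 | 0.226 | 0.055 to 0.397 | Yes |

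If every patient who died had residual filling on the procedure image, the LOCF FAS equals the second row. FAS and PPS would then disagree, and the plan would let the PPS (first row) decide for superiority.

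Planned case, survivors near 65% v 35%, same deaths:

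| Handling of deaths | Counts | Difference | 95% CI |
|---|---|---|---|
| Excluded | 37/57 v 21/61 | 0.305 | 0.133 to 0.477 |
| Failures | 37/62 v 21/62 | 0.258 | 0.088 to 0.428 |
| LOCF, all successes | 42/62 v 22/62 | 0.323 | 0.156 to 0.489 |

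All three lower limits lie above 0.

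**The case against.** Three stronger readings are tempting, and the documents support none of them.

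- **A reader might infer that deaths disappear from the mortality endpoint.** They do not. Serious adverse events are reported within 24 hours, mortality is compared between groups (Safety and efficacy assessment), and a treated patient with one safety evaluation stays in the safety set after withdrawal. What remains is narrower: the CRF duty for withdrawn patients covers only effects thought device-related, and the causality check names only the Tubridge, so ascertainment may be uneven.
- **A reader might infer that no primary analysis can ever score a death as a failure.** Under LOCF, a death with residual filling on the last image is a failure. The defect is that the score depends on that image and not on the death.
- **A reader might infer that living patients with an accident or fracture are abandoned.** Item 5 continues "When these fortuitous accidents occurs, including traffic accident, death,or bone fracture, et al., Close follow-up should be conducted", and the section requires contact attempts by telephone, letter or clinic interview.

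Other points deserve weight. If diverter-alone sacs cannot carry forward a complete grade, LOCF in the FAS would tend to favour the control arm, which is conservative for a superiority claim. That stands for the FAS, but the PPS is not protected: there the direction depends on which arm has more deaths. Deaths may also be few, since the earlier single-center study reported no procedure-related mortality and patients with limited survival are excluded. That limits the size and leaves the rule as it is.

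Finally, an article may leave the handling of death to a fuller document, and scoring it as non-occlusion is one choice among several. Here, however, the article does not stay silent: it classifies death and states what happens to that class.

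**Conclusion.** The point holds in this limited form. The withdrawal rules class death as a loss, in conflict with its status as an endpoint. Followed as written, the analysis rules give a patient who dies before the 6-month DSA a carried-forward occlusion status in the FAS and remove that patient from the PPS, which decides when the two differ. Deaths between the 6-month DSA and 1 year also remove patients whose primary outcome was observed.

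The size cannot be fixed from the documents. It is 1.6 points per re-scored death in an arm of 62. The conclusion can turn only in a borderline result, shown here under assumed deaths of 5 v 1 and survivor occlusion near 55% v 35%. At the planned 65% v 35%, the same deaths leave superiority intact under all three ways of handling them. The point is worth correcting because the repair is cheap; it is not evidence that the trial's result must be wrong.

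**What to change.** 1. Remove death from withdrawal item 5, and exempt it from the opening clause that withdraws every non-completer. Deleting it from item 5 alone would leave it covered by that clause.
2. Record every death in both arms, whatever its cause and whatever its suspected relation to a device, as a mortality event at its date.
3. In the FAS, score death before the 6-month DSA as not completely occluded, and do not apply LOCF to it.
4. Apply the same scoring in the PPS, so that death alone does not remove a patient, and keep in a patient with an observed 6-month DSA who dies later. A change to the FAS alone would not reach the deciding analysis.

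**Cost:** a few sentences and no extra data collection, best settled while recruitment is open (Trial status). Occlusion rates may be slightly lower in each arm, and some power may go. For example, assume 5% treatment-arm mortality, no control deaths and no other losses. The treatment rate becomes 0.65 × 0.95 = 0.6175, and power at 62 per arm falls from 0.93 to 0.86 (normal approximation without continuity correction), still above the planned 0.80.

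### For withdrawn patients the duty to record adverse events depends on judged device-relatedness, which conflicts with the all-cause safety endpoints and leaves events after withdrawal at risk of being under-counted

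*Protocol article*

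**What the plan says.** All references are to the protocol article.

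- **Withdrawal criteria, circumstances.** Item 2 reads "Occurrence of serious adverse events. The subjects, main researchers, ethics committee, supervisor or CFDA terminate the research based on the consideration of ethics". Item 3 reads "Early termination of the process based on the investigator’s judgment (to prevent development of severe complications, and so on". Item 4 reads "Significant deviation in implementation, or the subject failed to comply with the protocol". Item 5 covers loss to follow-up and accidents, "including traffic accident, death,or bone fracture, et al., Close follow-up should be conducted to determine their relationship with the usage of Tubridge FD".
- **Withdrawal criteria, closing paragraph.** The researcher tries to reach the withdrawn patient and documents why the patient left. On adverse effects, "those experienced adverse effects must be recorded in the CRF if the adverse effects were thought related to the devices used in this trial". It then adds: "All raw data of those enrolled and treated subjects must be kept including subjects withdrawn".
- **Primary and secondary outcomes.** Three safety endpoints are assessed at 30 days, 90 days and 1 year: morbidity or mortality overall, ischaemic stroke or intracranial bleeding, and "General adverse events (assessment time point: 30 days, 90 days and 1 year post-operation". None is limited to device-related events.
- **Safety and efficacy assessment.** Information is gathered at the procedure and at each follow-up point. Any adverse event is to be reported in detail, and a serious one needs a form and notification within 24 hours. No relatedness filter applies.
- **Planned analyses.** The safety set is every treated patient with one or more safety evaluations. Withdrawn patients who meet this stay in it.

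**The concern.** The endpoints count events from any cause. The recording duty for withdrawn patients is tied to a judgement of cause. The listed withdrawal circumstances are partly outcome-linked (items 2 and 3), so the patients in whom further safety events are plausible may be the ones who come under the conditional rule. Both devices are implants that remain in place, so leaving the study does not end exposure.

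Safety is part of the stated objective and of the hypothesis, and the Background asks whether haemorrhage and ischaemic complications are more frequent with flow diverters. If later strokes, bleeds or deaths in withdrawn patients go unrecorded because they were thought unrelated, the rates meant to answer that question are too low.

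**Working it through.** **1. The plan's own figures.** Inputs from Sample size: 35% against 65%, two-sided α = 0.05, power 0.80, up to 20% withdrawn.

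- Without continuity correction: n = [1.96·√(2·0.5·0.5) + 0.8416·√(0.35·0.65 + 0.65·0.35)]² / 0.30² = (1.386 + 0.568)² / 0.09 ≈ 42.4, so 43 per arm.
- With continuity correction: (42.4/4)·[1 + √(1 + 4/(42.4·0.30))]² ≈ 48.9, so 49 per arm and 98 in total, as stated.
- With withdrawals: 49/(1 − 0.20) = 61.25, so 62 per arm and 124 in total, as stated.
- Withdrawals allowed for: 0.20 × 62 = 12.4 per arm, or 24.8 of 124.

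The sample size reproduces. The safety point does not depend on it, but it supplies the 62 and the 20% used below.

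**2. The sections side by side.**

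| Section | Which events count or are recorded | Relatedness condition |
|---|---|---|
| Primary and secondary outcomes | Deaths and morbidity, stroke or bleeding, adverse events, to 1 year | None |
| Safety and efficacy assessment | Any adverse event; form for serious ones | None |
| Withdrawal criteria, closing paragraph | Adverse effects in withdrawn patients | Thought related to the trial's devices |
| Withdrawal criteria, item 5 | Accidents and deaths | Relation to the Tubridge only |

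For a withdrawn patient the first two rows and the third give different answers. The third and fourth also differ on which device is meant.

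**3. Which events are exposed.** An event that precedes withdrawal occurs while the patient is still under the general rule, so it should be on record. After withdrawal, the text asks that the patient be contacted and the reasons documented. It does not say that the 30-day, 90-day and 1-year assessments continue. The conditional rule is the specific one for these patients, so a site could reasonably follow it for later events.

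**4. Direction.** Let p be the true event risk, w the share of events falling under the withdrawn-patient rule, and u the share of those judged unrelated and left unrecorded. With the patient still in the denominator, the recorded risk is p·(1 − w·u), which cannot exceed p. The bias in each arm's rate is downward. Chi-square or Fisher tests on counts make no allowance for shortened follow-up.

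**5. Size, illustration only.** The document gives none of p, w or u. Assumed ranges: p = 5% to 15%, w = 0.2 to 1.0, u = 0.25 to 0.5. Then 1 − w·u runs from 1 − 1.0·0.5 = 0.50 to 1 − 0.2·0.25 = 0.95.

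| Assumed p | True events per 62 | Recorded events |
|---|---|---|
| 5% | 3.1 | 1.55 to 2.94 |
| 10% | 6.2 | 3.1 to 5.89 |
| 15% | 9.3 | 4.65 to 8.83 |

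The end w = 1.0 is an outer bound: it puts every event under the conditional rule, although the general rule should catch those before withdrawal. The end w = 0.2 corresponds to withdrawal at the planned maximum and unrelated to events. The loss is then 3.1·0.2·0.25 ≈ 0.16 to 9.3·0.2·0.5 = 0.93 events per arm, and less still if only events after withdrawal are counted.

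**The case against.** Much of the case on the other side stands.

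- A reader might infer that *only* device-related events are recorded after withdrawal. The text does not say so. It states a minimum duty and forbids nothing further.
- A reader might infer that the endpoints lose the serious events that lead to withdrawal. The general rule, with its 24-hour form, covers those events. Table 1 lists adverse events from the procedure to 1 year, the monitoring section asks for prompt reporting of any adverse event, and data already collected on withdrawn patients are kept.
- A reader might infer that a serious event withdraws the patient automatically. Item 2 can equally be read as a termination decision on ethical grounds after such an event, and the lead-in is limited to patients who cannot complete the study.
- A reader might infer that strokes and bleeds are recorded differently by arm. The CRF rule singles out no device. The Tubridge-only wording appears in item 5 and concerns the enquiry after accidents or death, for which it asks for closer follow-up, not less. This is an inconsistency, not evidence of differential recording.
- The endpoints affected are secondary, and the article condenses a fuller protocol.

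What these points do not remove is the conflict in the stated text. The general rule is tied to the procedure and the follow-up points, and the text does not say that withdrawn patients remain on that schedule. Keeping existing data does not collect later events.

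**Conclusion.** The point holds in limited form. The Withdrawal criteria conflict with the endpoint definitions and with the general reporting rule. Events after withdrawal are therefore at risk of incomplete recording that depends on a relatedness judgement, while the patients stay in the safety set denominator. Any resulting bias in event rates is downward.

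Its size cannot be computed from the document, which gives no event rate, no rate of withdrawal after an event and no share judged unrelated. Under the assumed ranges it runs from less than one event per arm to an outer bound of half the events, and that bound disregards the general rule. The direction of any effect on the difference between arms is unknown. The conclusion assumes that a site applies the withdrawn-patient rule as written to later events. The primary endpoint's test and sample size are untouched.

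**What to change.** Reconcile Primary and secondary outcomes, Withdrawal criteria, and Safety and efficacy assessment.

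1. Separate withdrawal from treatment or from protocol adherence from the end of data collection. This takes no position on when treatment should stop.
2. As far as valid consent and any ethics or regulatory termination allow, continue the contacts already scheduled to 1 year for patients who meet a withdrawal circumstance.
3. Replace the conditional CRF sentence with a duty to record all deaths, strokes, bleeds and adverse events in both arms, whatever their judged relatedness.
4. Reword item 5 so that relatedness to the assigned device is assessed in both arms.

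The cost is a wording amendment and slightly more site follow-up work, because Planned patient follow-up already provides for clinic or telephone contact. Recruitment is open, so the change should be made soon: events not recorded at the time may not be recoverable.
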